**Methods:**

The study employs a cluster-randomized controlled crossover design with four intervention groups. Participants will be randomly assigned to one of four groups: a combined exercise and guided environmental intervention (physical activity-promoting culture), an exercise intervention, a guided environmental intervention, or a non-guided environmental intervention. The exercise intervention involves group-based sessions twice a week, while the environmental intervention focuses on implementing PA into daily routines. The guided environmental intervention is equivalent to the non-guided one but provides additional support two to four times weekly. We aim to recruit at least 120 participants from six nursing homes. Each facility will receive two interventions in a 16-week crossover design (36 weeks in total, including weeks for measurements), followed by a 16-week non-guided environmental intervention (follow-up phase). Primary outcomes include steps per day as an indicator of PA behavior, and the Short Physical Performance Battery (SPPB) to assess physical functioning.

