### Trial design

Based on existing research and the physical exercise recommendations mentioned above, this monocentric intervention study is conducted through a controlled cluster-randomized crossover design with four arms. The four interventions are randomly paired and ordered using MATLAB (‘nchoosek’ and ‘randperm’ functions), ensuring that each intervention will be combined with each of the other three interventions once. These six different intervention combinations were then clustered randomized to the nursing homes in the agreed order. In general, the trial design can be divided into an intervention and a follow-up phase with four separate weeks of measurements (t1-t4). So t1 is the baseline measurement time point, t2, with a double role, corresponds to the post-measurement point for the first intervention as well as the pre-measurement point for the second intervention phase. According to this, t3 will be the post-measurement point for the second intervention. 16 weeks after t3, the study will be concluded with the follow-up measurements (t4) after 52 weeks (see Figure 1). The date of first enrollment was August 2022.

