### Statistical analysis

The descriptive statistics will be presented as either group mean values and standard deviations/errors or medians and interquartile ranges, depending on the distribution of the outcome measures. The intervention effect for the primary outcomes (Number of Steps and SPPB) will be analyzed separately using a 4 (between group: PA-promoting culture intervention, guided environmental intervention, non-guided environmental intervention, or exercise intervention) × 2 (within test time point: t1:t2, and t2:t3) linear mixed model, where participants can be nested within nursing homes and be calculated as a random effect. The Follow-Up effects will be analyzed additionally using a 4 (between group: all interventions) x 3 (within test timepoint: t1/t2 – t2/t3 – t4). If baseline differences are found, the baseline assessment values, as well as age and sex discrepancies, will be included as covariates in the statistical model. In cases of statistically significant interaction effects, Bonferroni-adjusted *post hoc* tests (such as t-tests or Wilcoxon tests) will be employed to identify significant differences between groups from baseline to post-allocation testing. The data will be pre-processed and analysed using SPSS.

The effect size will be determined using Cohen’s f, which indicates the magnitude of treatment effectiveness and helps assess whether a statistically significant difference is practically significant (Cohen and Ebl, 1988). Cohen’s f values are classified as small (0 ≤ f ≤ 0.24), medium (0.25 ≤ f ≤ 0.39), or large (f ≥ 0.40) (Grissom and Kim, 2011). For *post hoc* analysis, Cohen’s d effect size will be calculated. Additionally, PSdep scores (probability of superiority for dependent samples) will be calculated as an estimate of effect size in non-parametric *post hoc* tests. The significance level will be set at p < 0.05. An intention-to-treat analysis will be conducted, considering all participants in the groups to which they were randomly assigned, regardless of whether they received or adhered to the assigned intervention. We will control participation in the interventions to analyze the effect of the intervention in more detail. Multiple imputations will be used to handle missing data, assuming that the missingness is random. If more than 40% of participants are lost to outcome assessment or demonstrate insufficient participation in training sessions, an additional per-protocol analysis will be conducted.

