When residents are mobile, able to take care of themselves, and challenged and encouraged in their environment, they might become more physically active (den Ouden et al., 2017). Staying active is believed by many older adults to enrich their overall life experiences (Guell et al., 2016; Halaweh et al., 2018), and data from Sococco et al. shows that only 5.9% of residents move into a nursing home based on their own decision (Scocco et al., 2006). However, the decrease in obligations as well as physical and cognitive limitations that often come along with moving into a nursing home can lead to immobility and dependence on others, as well as an increase in sedentary behavior. As seniors become sedentary and less physically active, their physical and cognitive abilities often decline rapidly (Auerswald et al., 2020). Due to spending most of their time in one place, typically their room (Jansen et al., 2017), their spatial orientation abilities also decrease (Wollesen et al., 2020a), leading to isolation, loneliness, and depression (Antoniewicz and Brand, 2016) and a decline in quality of life (Saajanaho et al., 2016; Duppen et al., 2020). Most studies that have examined the effects of physical exercise on these health outcomes (Fiatarone et al., 1990; Crocker et al., 2013; Johnen and Schott, 2018; Cordes et al., 2019) have revealed that multicomponent training can affect physical and cognitive outcomes, such as walking, balance, dual-tasking abilities, and wellbeing (Wollesen and Voelcker-Rehage, 2014). Furthermore, maintaining physical functioning related to ADLs can promote independence (Saajanaho et al., 2015). This, in turn, could relieve the burden on nurses and reduce the gap in demand between care and nurses, especially given the current nursing shortage. Exercise interventions in nursing homes are typically conducted twice a week for about 1 hour each session (Cordes et al., 2021a). However, engaging in PA only twice a week for about 45–60 min may not promote residents’ daily PA behaviors and their LSM, and it may not reduce the time they spend sitting in one place: Nursing home residents spend most of their time sitting regardless of whether they participate in group sessions once or twice a week (Auerswald et al., 2020). Thus, the unique contribution of PROGRESS is to combine an exercise intervention with an environmental intervention. We assume that both making changes in the nursing home environment and having residents participate in exercise classes will contribute to residents’ physical functioning, PA, and mobility (Broers et al., 2017; Blaga et al., 2018; Kwan et al., 2020; Hernandez et al., 2023). While the exercise intervention aims to have participants practice certain physical and cognitive functions based on well-known exercise principles, such as intensity and progression, the environmental intervention is particularly aimed at removing obstacles in the environment that residents face. Since this intervention equips the entire nursing home with exercise stations, PROGRESS may reduce nursing home residents’ sedentary behavior and improve their LSM. Further, both types of interventions aim to help residents establish new social contacts. Also, because motivational factors are important determinants of exercise participation and PA, we follow a participatory approach to make sure participants are interested in engaging in these behaviors, overcoming motivation barriers. An additional unique aspect of PROGRESS is its follow-up phase, which will last for 16 weeks after the intervention is completed (after t3, week 37–53). This phase aims to evaluate the program’s sustainability and related changes in primary and secondary outcomes. (Fiatarone et al., 1990; Crocker et al., 2013; Johnen and Schott, 2018; Cordes et al., 2019). It is expected that during the follow-up period, the primary and secondary outcomes will worsen but not return to the baseline level.

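### The primary model uses t2 as both outcome and baseline and names no phase or home-by-phase term, so its error rate and estimates rest on unstated assumptions

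*Protocol article*

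**What the plan says.** Under Statistical analysis, each primary outcome (steps per day, SPPB) gets a linear mixed model with intervention as a four-level between-group factor and time as a two-level within factor: "2 (within test time point: t1:t2, and t2:t3) linear mixed model, where participants can be nested within nursing homes". The random part is "where participants can be nested within nursing homes and be calculated as a random effect". The follow-up model is a four-group design "x 3 (within test timepoint: t1/t2 – t2/t3 – t4", in which t1 or t2 is the pre value, t2 or t3 the post value, and t4 the follow-up.

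Trial design confirms the dual use: "t2, with a double role, corresponds to the post-measurement point for the first intervention as well as the pre-measurement point" for the second phase. It also says that each intervention is combined once with each of the other three, giving six pairs for six homes. The Abstract gives the timing: "Each facility will receive two interventions in a 16-week crossover design (36 weeks in total, including weeks for measurements". No washout is described.

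Baseline value, age and sex enter as covariates only if baseline differences are found. If the interaction is significant, Bonferroni-adjusted "tests (such as t-tests or Wilcoxon tests) will be employed to identify significant differences between groups from baseline to post-allocation testing".

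**The concern.** The model fits a trial in which four separate groups are each measured before and after. Here every resident receives two interventions and every intervention is delivered to a whole home. Four things follow.

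- **Double use of t2.** A high t2 value raises the change credited to the first intervention and lowers the change credited to the second. A model with independent residuals does not know this.
- **No home-by-phase term.** Resident and home intercepts cancel from a pre-post change. Whatever happens to one home between two occasions does not cancel, and it is the natural error term for an intervention given to that home. The stated model has no place for it.
- **No phase term.** Each pair occurs in one order only, and each intervention is in three homes, so it can never be split evenly between phases. The limitations paragraph itself concedes natural fluctuations and contextual factors.
- **t2 as baseline.** With no washout described, t2 cannot be assumed to be a clean baseline for the second intervention.

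The example post hoc tests ignore the homes altogether. At stake are the p-values and contrasts for both primary outcomes. The article calls about 1.0–1.3 SPPB points clinically meaningful, so a shift of a few tenths matters.

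**Working it through.** **Inputs from the article.** Six homes; 10–20 residents each (120/6 = 20); six pairs used once; r = 0.60; significance at p < 0.05; two 16-week phases, so 2 × 16 = 32 of the 36 weeks.

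**Inputs that are assumptions.** Home variance of 5% of the total; home-by-occasion variance of 0 to 5%; the correlation pattern over three occasions (the article gives one r, for two measurements).

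**Step 1: the two changes are linked.** With unit variances, Cov(t2−t1, t3−t2) = r12 + r23 − r13 − 1. The variance of each change is 2(1 − 0.60) = 0.80.
- Exchangeable: 0.60 + 0.60 − 0.60 − 1 = −0.40; correlation −0.40/0.80 = −0.5.
- AR(1): 0.60 + 0.60 − 0.36 − 1 = −0.16; correlation −0.16/0.80 = −0.2.
- Random walk: 0.

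**Step 2: false-positive rate.** Trials with no treatment effect were simulated and the stacked model fitted by REML (random intercepts for home and resident), testing group × time at 5% with 20 residents per home.

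| Home-by-occasion variance | Exchangeable | AR(1) | Random walk |
|---|---|---|---|
| 0 | 13–14% | 7% | 4% |
| 1% | 25–30% | 20% | 29% |
| 2% | 41–43% | 37% | 47% |
| 5% | 66–68% | 60% | 71% |

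With exchangeable correlation and zero home-by-occasion variance, giving each phase its own separate t2 measurement brings the rate to 4%. The excess in that cell therefore comes from the double entry. Adding phase terms to the stacked model leaves 12%, 38% and 64% at variance 0, 2% and 5%.

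**Step 3: the other reading.** If the two levels are the two phases and the outcome is change per phase, a phase term is present. The rate is then about 7% at zero variance, 29% at 2% and 57% at 5%.

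**Step 4: dependence on order.** Let the true effects relative to untreated be 1.0 for the combined intervention (I1), 0.5 for exercise (I2), 0.5 for guided environmental (I3) and 0 for non-guided (I4). If a fraction c of the first effect A remains at t3, the phase-1 change is A and the phase-2 change is B − (1 − c)A. The planned I1−I4 contrast is the mean change over the three I1 homes minus that over the three I4 homes.

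- No carry-over (c = 0), highest: I1 always first, mean 1.0; I4 always second, mean (−1.0 − 0.5 − 0.5)/3 = −0.67; contrast 1.67.
- No carry-over, lowest: I1 always second, mean (0.5 + 0.5 + 1.0)/3 = 0.67; I4 always first, mean 0; contrast 0.67.
- Half carry-over, highest: 1.0 − (−0.5 − 0.25 − 0.25)/3 = 1.33.
- Half carry-over, lowest: (0.75 + 0.75 + 1.0)/3 − 0 = 0.83.
- Full carry-over: the phase-2 change equals B, so the contrast is 1.00 in every order.

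Over the 2^6 = 64 possible orders, each extreme occurs in 2. The 10th to 90th percentile range is 0.83–1.50 with no carry-over and 0.92–1.25 with half.

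**Step 5: a common phase effect.** With no treatment effect and a 0.3 SD change in phase 1 only, the largest false contrast is about 0.1 SD in a best-balanced order and about ±0.3 SD in the two opposite extreme orders. Only 24 of the 64 orders have the best balance; in another 24, one intervention is always first and another always last.

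**The case against.** The case for the plan has several fair parts.

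- **Reading.** The levels t1:t2 and t2:t3 can be read literally as the two phases. That reading contains a phase term and nearly holds its level at zero home-by-occasion variance. But the follow-up coding favours the stacked reading. Under the phase reading, the interaction that triggers the post hoc tests would be intervention × phase, which is not the intervention effect, and home-by-phase variation would still be missing.
- **Condensed article.** Degrees of freedom and covariance structure are commonly left to an analysis plan, and the nesting wording is permissive. This stands for those details. It does not cover the model that the article does fix.
- **Post hoc tests.** They are given as examples, are Bonferroni-adjusted and are conditional on a significant interaction. This stands; they are a secondary part of the point.
- **Carry-over.** A reader might take the Discussion's expectation that "the primary and secondary outcomes will worsen but not return to the baseline level" as the plan's own evidence that effects outlast an intervention. It is not: the follow-up phase is itself the non-guided environmental intervention, so the sentence does not describe persistence after stopping. The point rests only on the absence of a described washout.
- **Unbiased case.** If effects persist fully, the planned contrast is exactly right in every order, and the usual crossover model is the one that is biased. This stands and must be disclosed with the fix.

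**Conclusion.** The structural fault holds on the article's own text: t2 is used twice, intervention is called a between factor although each resident receives two, and neither a phase nor a home-by-phase term is named in a design with six homes and one order per pair.

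A reader might infer that the false-positive rate is far above 5% whatever the data look like. The documents do not support that. They give no home-by-occasion variance and no three-occasion correlation pattern. At zero variance the rate is 4–14%; it reaches 20–30% at 1% of total variance, 37–47% at 2% and 60–71% at 5%. The safe statement is that the test loses its level once homes drift even slightly differently between occasions, under either reading examined.

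Nor are the estimates wrong in every case. They depend on the order drawn unless effects persist fully, and the 0.67–1.67 and 0.83–1.33 ranges are extremes under the assumed effects. The model should be respecified before analysis.

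**What to change.** Enter each occasion once: t2 and t3 as outcomes and t1 as covariate; fixed effects for intervention and phase; random effects for home, home × phase and resident; small-sample degrees of freedom. An equivalent analysis of home-occasion means would also serve. A version with home, occasion and intervention terms (18 means − 6 − 2 − 3 = 7 error df) had simulated false-positive rates of 5.2%, 5.1% and 6.1% at home-by-occasion variance 0, 2% and 5%. A phase term alone is not enough.

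Take the four hypothesised contrasts (I1 vs I2, I1 vs I3, I2 vs I4, I3 vs I4) from this model with multiplicity adjustment, in place of the t and Wilcoxon tests.

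State that the model assumes no carry-over. With the effects in Step 4 and a correlation of 0.5 between a home's two phase means, a true 1.0 is estimated as 0.77–0.98 with half carry-over and 0.54–0.96 with full; at a correlation of 0.9 the ranges are 0.61–0.93 and 0.22–0.86. Prespecify a sensitivity analysis with a term for the preceding phase. Keep that term simple, because there are only 12 home-phase means.

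The cost is a rewritten model specification and wider confidence intervals. No new data are needed.

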## Abstract

**Background:**

Nursing home residents’ health and psychosocial well-being may be influenced by their often-sedentary lifestyles, which arise due to physical barriers like steps, an unwelcoming environment, limited awareness of the importance of physical activity (PA), and a lack of orientation. While exercise interventions are important for maintaining or improving physical and cognitive functions, they may not help increase daily PA behavior. Therefore, the PROGRESS study aims to investigate the short- and long-term effectiveness of tailored and combined physical exercise and environmental interventions for improving PA behavior and physical functioning among nursing home residents.

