### Non-guided environmental intervention

The non-guided environmental intervention will use the same materials as the guided environmental interventions. However, this intervention will not be supervised or guided, so participants must engage independently, with the assistance of nursing home employees or relatives. This non-guided environmental intervention also serves as the follow-up condition between t3 and t4 (see Table 2).

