### Sample size estimate/power calculations

Statistical power analysis was conducted to estimate the sample size to test our hypothesis in G*Power (Version 3.1.9.4, Heinrich Heine University of Duesseldorf) (Faul et al., 2009). The following input parameters were used to obtain small-sized test × group interaction effects within an ANOVA: effect size (*f* = 0.15) (i.e., a small effect, (Tudor-Locke et al., 2011), type I error (α = 0.025), type II error (1-β = 0.8), number of groups (n = 4), number of measurements (n = 2), correlation between measurements (r = 0.60).

The size of the estimated sample to generate sufficient power to achieve the small effect is N = 88. To compensate for the estimated dropout rate of 30% (e.g., 20% lost to follow-up; plus 10% mortality) we plan to include a total of N = 116 participants. Based on the study design, we will integrate N = 29 participants in each condition.

Regarding the special cohort, recruiting approximately 30 participants per intervention arm per nursing home seems unrealistic, so multiple nursing homes will be needed for each intervention arm. As the number of nursing homes is also limited, each one needs to take on more than one intervention arm to reach a total of ∼30 participants. By the life expectancy of the special cohort and for ethical reasons, we have limited the maximum study duration to 1 year per participant. This means that each participant can complete two intervention phases and one follow-up phase per year, nested in a nursing home. In terms of the four intervention arms, this means six different possible combinations (this means six different nursing homes), each with 10–20 nursing home residents participating in the study.

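### The 4×3 follow-up model compares four interventions at t4, but each resident's single t4 value follows two interventions plus a common non-guided phase and cannot be attributed to one of them

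*Protocol article*

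**What the plan says.** All references are to the protocol article.

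- **Aim.** The Abstract (Background) sets out to study the "short- and long-term effectiveness of tailored and combined physical exercise and environmental interventions".
- **Two interventions per resident.** The Abstract (Methods) says: "Each facility will receive two interventions in a 16-week crossover design". The sample size section adds that "each participant can complete two intervention phases and one follow-up phase per year, nested in a nursing home". Under Trial design, each intervention is paired once with each of the other three. That gives six pairs for six homes and three homes per intervention.
- **Measurements.** Of the second time point, Trial design says: "t2, with a double role, corresponds to the post-measurement point for the first intervention as well as the pre-measurement point for the second intervention phase". Of the last: "16 weeks after t3, the study will be concluded with the follow-up measurements (t4) after 52 weeks". There is one t4 measurement per resident.
- **Condition before t4.** "This non-guided environmental intervention also serves as the follow-up condition between t3 and t4" (Non-guided environmental intervention). This is also the fourth study arm.
- **Follow-up model.** Statistical analysis states: "The Follow-Up effects will be analyzed additionally using a 4 (between group: all interventions) x 3 (within test timepoint". With the time levels, the specification reads "4 (between group: all interventions) x 3 (within test timepoint: t1/t2 – t2/t3 – t4". It comes in addition to the primary 4×2 model. As stated, it has no term for the other intervention that the resident received.
- **Expected course.** The Discussion expects outcomes to decline during follow-up without falling all the way to baseline.

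**The concern.** In the time factor, the first two levels are slashed pairs: the pre value is t1 or t2 and the post value is t2 or t3, according to the period in which the intervention was given. The third level, t4, has no alternative. If a home received A and then B, the same t4 value is therefore the natural follow-up entry for A and for B.

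For B, t4 comes 16 weeks after the intervention ended. For A, it comes after a further 16-week intervention as well. For the non-guided intervention given second, the phase before t4 is a continuation; for any other intervention given second, it is a switch to a different arm.

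This model is the only stated route to the long-term aim. Followed as written, it would report under one intervention's name a follow-up result produced partly by another.

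**Working it through.** The article gives no figure for the follow-up analysis, so there is none to reproduce. The check is structural, with a numerical illustration.

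**1. Timing.** t4 is at week 52 and t3 is 16 weeks earlier: 52 − 16 = 36. If the two phases are equally long, t2 is near week 36/2 = 18. For the first intervention, t4 then comes about 52 − 18 = 34 weeks after it ended.

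**2. Records.** On the pre/post/follow-up reading, a resident given A then B contributes two rows:

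- A: (t1, t2, t4)
- B: (t2, t3, t4)

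With the planned 116 residents, this is 2 × 116 = 232 rows but only 116 distinct t4 values. Dropout lowers both counts and leaves the doubling.

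**3. Contrasts within a home (A then B).**

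- t4 level, A minus B: t4 − t4 = 0, whatever the truth.
- Post to follow-up: (t4 − t2) − (t4 − t3) = t3 − t2, the change during B. The better B works, the better A appears to be maintained.
- Pre to follow-up: (t4 − t1) − (t4 − t2) = t2 − t1, the change during A.

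In both change contrasts t4 cancels. This is algebra and needs no assumption about persistence. A participant random effect models the correlation between the two rows; it cannot turn one measurement into two.

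**4. Contrasts across homes.** Label the interventions 1 to 4. The pairs are 12, 13, 14, 23, 24 and 34; write y for a home's mean t4 effect. Using simple means with equal home sizes (a mixed model would weight differently):

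- Mean for 1 = (y12 + y13 + y14)/3
- Mean for 2 = (y12 + y23 + y24)/3
- Difference = (y13 + y14 − y23 − y24)/3; the shared home drops out.

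Suppose intervention 1 has a lasting effect of 1 and the others 0. The persistence weights below are assumptions, because the article gives none.

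| Weight of first / second intervention at t4 | Difference, 1 minus 2 (true value 1) |
|---|---|
| 1 / 1 | (1 + 1)/3 = 0.67 in every order |
| 0.5 / 1 | from (0.5 + 0.5)/3 = 0.33 to (1 + 1)/3 = 0.67, by order |
| 0 / 1 | from 0 to 0.67, by order |

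In the first row the group means are 1, 1/3, 1/3 and 1/3, so each ineffective intervention is credited with a third of the effect of the effective one.

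**5. Can a model separate the two?** Giving each intervention its own t4 effect in first and in second position needs 1 + 3 + 3 = 7 parameters, against six home means. It cannot be estimated.

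**6. The other reading of the notation.** The three levels could instead mean phase 1, phase 2 and follow-up, so that each t4 value enters once. The four-level group factor then has no clear value at t4: the resident has had A and B and is now under the non-guided condition, like everyone else. Attribution to one intervention still fails.

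**The case against.** The strongest reply has four parts.

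- **Double use is inferred.** The article does not say in words that t4 is entered twice, and an analysis plan that is not shown may define the data layout. This stands, and it limits the count of 232 rows to one reading. The pre/post/follow-up reading fits the slashes and the two-measurement power calculation better, and the phase reading does not remove the attribution problem.
- **Follow-up may be meant for the whole programme.** The model is run in addition to the main one, the stated comparative hypotheses name no contrast at t4, and the Discussion speaks of the sustainability of the programme. This also stands and limits the weight of the point. A programme-level question does not, however, need a model with four intervention groups.
- **The pairing is balanced.** Under equal additive persistence the direction of a contrast survives, at two thirds of its size. A reader might infer that the follow-up results would be meaningless or that every contrast is zero. The documents do not support that: only the within-home t4 level contrast is zero by construction. The rest is contaminated, by an amount that depends on unknown persistence.
- **Order is already fixed.** A reader might compute that one intervention came first in all its homes with probability 4 × (1/2)³ = 0.50. That assumes an independent, even draw of order within each pair, which the article does not describe. It also reports the allocation to homes as already made. The figure is a prior probability and no evidence about this trial; the realised order can simply be looked up.

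**Conclusion.** The point holds in this form: one t4 value per resident, taken after two interventions and a common non-guided phase, cannot support a four-intervention follow-up comparison. The cancellation of t4 from within-home contrasts follows from the design and the pre/post/follow-up reading alone. The shrinkage from 1 to 0.67, or to as little as 0, rests on assumed persistence weights and simple home means, and is an illustration. It should be settled before analysis, because long-term effectiveness is a stated aim. A reader might extend the criticism to the primary 4×2 analysis, but that model does not use t4, so this point leaves it untouched.

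**What to change.** Replace the 4×3 intervention-by-time follow-up model as follows.

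1. Use each t4 value once.
2. Report the changes from t1 to t4 and from t3 to t4 for the whole programme, and descriptively by sequence, that is, by home.
3. Describe the result as maintenance under non-guided conditions, and make no long-term claim for a single intervention.
4. Label as exploratory any model by second-phase intervention or additive in both interventions received. With six homes, each leaves at most a few home-level degrees of freedom: 6 − 4 = 2 for the additive model, and likewise for the other if all four interventions occur in the second phase. Adjusting such a model for t3 would also condition on a value already affected by the second intervention.

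This changes wording and analysis only and needs no new data. The cost is a narrower long-term claim: a before-after description of the programme, subject to the lack of a traditional control group that the Discussion already concedes.
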